### Objectives {7}

Building on the study by [name] et al. [35], the current study aims to investigate whether EMDR therapy is more effective in comparison to a waiting list control condition.

#### Hypothesis 1

EMDR therapy is associated with a significant decrease in severity of depressive symptoms and decrease in percentage of patients meeting DSM-5 criteria for MDD compared to the waiting list.

Outcome measures: Total score on the CDI-2 and the percentage of patients meeting DSM-5 criteria for MDD (K-SADS-PL-5).

#### Hypothesis 2

After treatment with EMDR, participants report less comorbid PTSD, anxiety and social/emotional symptomatology in comparison to those in the waiting list control condition.

Outcome measures: severity of PTSD (CATS), anxiety (SCARED) and social/emotional symptoms (SDQ).

The second aim of this study is to investigate predictors of treatment outcome. We will test the following predictors: baseline PTSD symptoms (CATS), family functioning (FAD) and experienced emotional abuse or emotional neglect in childhood (CTQ).

#### Hypothesis 3

A higher level of post-traumatic stress symptoms at baseline predicts a stronger post-treatment reduction in depressive symptoms.

Outcome measures: reduction of depressive symptoms (CDI-2 total score), severity of post-traumatic stress symptoms (CATS total score).

#### Hypothesis 4

A higher level of family dysfunction at baseline predicts smaller post-treatment reductions of depressive symptomatology.

Outcome measures: severity of depressive symptoms (CDI-2 total score), family functioning (FAD, general functioning score and dimension scores).

#### Hypothesis 5

A higher level of emotional abuse or neglect at baseline predicts smaller post-treatment reductions of depressive symptomatology.

Outcome measures: reduction of depressive symptoms (CDI-2 total score), experience of emotional abuse or neglect (respective subscales CTQ).

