##### Family functioning

The Dutch version [52] of the Family Assessment Device (FAD; Child and Parent Version) [53] is used to assess structural, organizational and transactional characteristics of families. The questionnaire covers 6 dimensions: affective involvement, affective responsiveness, behavioural control, communication, problem solving and roles. In addition, there is a 7th scale measuring general family functioning. Both dimension scores and the general functioning scale are used in the analyses. The FAD comprises 60 items rated on a 4-point scale. Scale scores are computed by adding the responses and dividing by the number of items in the scale with higher scores indicating worse levels of family functioning. The psychometric qualities of the English version have been studied extensively and were satisfactory to good [53, 54]. Results from studies on the Dutch version [55] were comparable.

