### Sample size {14}

A power analysis is calculated with G-Power. With the following assumptions: ANOVA with 2 groups and (EMDR and waiting list), 2 points of measurement (baseline and after treatment), the CDI-2 total score as outcome measure, effect size of F = 0.40, a power of 0.095 with *α* = 0.05, a total of 48 participants (24 participants per group) will be needed. In line with the drop-out rate (21.6%) we had in our first clinical study [35] and by those reported in previous intervention studies using EMDR with MDD patients (23% [26], 30% [29], 15% [30]), a maximum of 30% drop-out during treatment and follow-up trajectory is expected. Consequently, 64 adolescents will be included in the study, equally divided between EMDR and waiting list condition.

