#### Primary study parameter(s)

To investigate the effect of EMDR and waiting on the primary outcome (level of depressive symptoms, CDI-2) and secondary outcome variables (i.e. post-traumatic stress symptoms (CATS), anxiety symptoms (SCARED) and overall social-emotional problems (SDQ)), a linear mixed model analysis will be conducted. A chi-square test will be used to investigate whether there is a difference between conditions in the percentage of MDD diagnoses (K-SADS-PL; MDD, partial remission, full remission) at T1, comparing changes in the waiting list condition (T0–T1; *n* = 32) with changes in the EMDR condition (T0 (*n* = 32) + T0WL(*n* = 32) − T1).

Effect sizes will be calculated using Cohen’s *d.* Based on the mean difference between scores from baseline (T0) to post-treatment (T1) and from baseline (T0) to follow-up (T2, T3), the results will be divided by the pooled standard deviation (Cohen, 1988).

To investigate the predictive effect of baseline post-traumatic stress symptom severity (CATS), emotional abuse and emotional neglect (CTQ), and general family functioning (FAD) on treatment outcome, we will perform a linear mixed model analysis. All predictors will be entered separately and we will conduct Bonferroni post hoc corrections to correct for the number of analyses. The level of significance will be set at *α* = 0.05/4.

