#### Other study parameters

For the prediction analyses, all treated participants, including participants from the former waiting list control group, will be combined. The four predictor variables (baseline post-traumatic stress symptom severity (CATS), emotional abuse, emotional neglect (CTQ) and general family functioning (FAD) scores will be entered separately in the linear mixed model analyses. Bonferroni post hoc corrections will be conducted in order to correct for the number of analyses. The level of significance will be set at *α* = 0.05/4.

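### The four predictor tests use a fixed Bonferroni level of 0.05/4, which is valid; Holm's step-down keeps the same 5% familywise error, never rejects less, and gains power if several predictors are real

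*Protocol article*

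**What the plan says.** The predictor analyses appear twice under Statistical methods {20a} in the protocol article.

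- *Primary study parameter(s)*: "All predictors will be entered separately and we will conduct Bonferroni post hoc corrections to correct for the number of analyses". The next sentence sets the threshold: "The level of significance will be set at *α* = 0.05/4".
- *Other study parameters*: the same rule again, "Bonferroni post hoc corrections will be conducted in order to correct for the number of analyses", with the same 0.05/4. This paragraph lists the four predictors: baseline CATS severity, CTQ emotional abuse, CTQ emotional neglect, and "general family functioning (FAD) scores will be entered separately in the linear mixed model analyses". It also defines the analysis set: "all treated participants, including participants from the former waiting list control group, will be combined".

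The tests serve the second aim in Objectives {7}, which states three directional hypotheses. Hypothesis 3, for example, reads "A higher level of post-traumatic stress symptoms at baseline predicts a stronger post-treatment reduction in depressive symptoms". Hypothesis 5 covers both CTQ subscales, so three hypotheses give four tests. No step-down or other sequential procedure is named. Sample size {14} rests on the CDI-2 group comparison alone and gives no power or effect size for the predictors.

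**The concern.** Under a fixed Bonferroni rule every predictor must reach p ≤ 0.0125, whatever the other three tests show. Once one null hypothesis has been rejected, only three can still be falsely rejected, so dividing by four spends less than the available 5%. Holm's procedure uses what is left. It compares the ordered p-values with 0.05/4, 0.05/3, 0.05/2 and 0.05, stopping at the first failure. It needs no assumption beyond those Bonferroni makes.

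At stake is the power for the second, third and fourth predictor. The sample was not sized for these tests, and the protocol expects all three hypotheses to be true. Several real predictors at once is the setting in which the two methods differ most. A true predictor with a p-value between 0.0125 and its Holm threshold would be reported as not significant under the stated rule and as significant under Holm.

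**Working it through.** **Step 1. Reproduce the stated level.** 0.05/4 = 0.0125. The sum bound is 4 × 0.0125 = 0.05. If the tests are independent, familywise error is 1 − (1 − 0.0125)^4 = 0.0491. The plan's figure is right.

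**Step 2. Compare thresholds.**

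| Ordered p-value | Bonferroni | Holm |
|---|---|---|
| smallest | 0.0125 | 0.05/4 = 0.0125 |
| second | 0.0125 | 0.05/3 = 0.0167 |
| third | 0.0125 | 0.05/2 = 0.025 |
| largest | 0.0125 | 0.05 |

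No Holm threshold is below 0.0125, so Holm rejects everything Bonferroni rejects. The first thresholds are equal, so the two methods agree exactly on whether anything is rejected.

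**Step 3. Inputs for power.**

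- From the document: "64 adolescents will be included in the study", both arms pooled once treated, so at most n = 64. Sample size {14} expects at most 30% drop-out: 64 × 0.70 = 44.8, about 45.
- Assumed, because the document gives no value: each real predictor correlates r = 0.3 with CDI-2 reduction. Tests are two-sided (sidedness is not stated). The test of a correlation stands in for the mixed-model term.

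**Step 4. Power of a single test at 0.0125.** The non-centrality is atanh(r) × √(n − 3), and the two-sided critical value is 2.498.

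- n = 64: atanh(0.3) × √61 = 0.3095 × 7.810 = 2.417. Power = P(Z > 2.498 − 2.417) = P(Z > 0.080) = 47%.
- n = 45: 0.3095 × √42 = 0.3095 × 6.481 = 2.006. Power = P(Z > 0.492) = 31%.

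**Step 5. Holm by simulation.** Sets of four z-statistics with these non-centralities, either independent or mutually correlated 0.4, give average power per true predictor:

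| n | Real predictors | Bonferroni | Holm |
|---|---|---|---|
| 64 | 4 | 47% | 55% |
| 64 | 3 | 47% | 51% |
| 64 | 2 | 47% | 49% |
| 64 | 1 | 47% | 47% |
| 45 | 4 | 31% | 36-37% |

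With one real predictor the gain is 0.2 points or less. A separate simulation that drew predictors and outcome directly, with predictors correlated 0, 0.3 or 0.5, agrees to within about a point (47% vs 56% at n = 64 with four real).

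**Step 6. Other quantities.**

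- At least one significant predictor: identical under both rules in every scenario, as Step 2 requires.
- All four significant, n = 64, r = 0.3, all real: about 5% vs 18% (independent statistics) and 15% vs 32% (correlated 0.4).
- Stronger effects, r = 0.4, all four real: about 80% vs 87-90% per predictor at n = 64, and 60% vs 70-72% at n = 45.
- Familywise error with no real predictor: at most 5.0% and the same for both methods. With some real and some null predictors, Holm stays at or below 4.8%.

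**The case against.** The strongest reply is that nothing here is wrong. Bonferroni at 0.05/4 is a pre-specified, valid rule with correct arithmetic, and both statements of it agree. That stands in full. A reader might infer that the plan contains a multiplicity error; on the four predictors it counts, it does not.

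A reader might also infer that Hypotheses 3 to 5 lose power for nothing, by as much as the all-four-real case suggests. The document does not support that. It gives no effect size for any predictor, and expecting three hypotheses to hold does not make four equal effects likely. The loss arises only after another predictor has been rejected. It shrinks to about 2 points with two real predictors and practically vanishes with one. At n = 45 and r = 0.3 most true predictors would be missed under either rule, so sample size limits these tests more than the correction does.

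Single-step Bonferroni also has an advantage: one fixed threshold and simple simultaneous confidence intervals. That is real but small, and the article plans no such intervals.

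The tests are also not central to the trial. The abstract describes the predictor question as exploration, and the treatment comparisons are unaffected.

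Finally, Holm does not settle how many tests the family contains. Under *Family functioning* the article says "Both dimension scores and the general functioning scale are used in the analyses", and Hypothesis 4 also lists the dimension scores, while the statistical section counts only the general scale. Adding the six dimensions would make ten tests, and 10 × 0.0125 = 12.5% as the error bound. That is a separate question. Holm over four tests would not cure it, although Holm improves on Bonferroni for any family size.

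**Conclusion.** The point holds as an optional improvement to a second-aim analysis. The fixed 0.05/4 rule is valid but needlessly conservative after the first rejection. Holm gives the same 5% familywise guarantee under any dependence and is never less powerful.

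At r = 0.3 the gain per true predictor at n = 64 is about 8 points with four real predictors, about 4 with three, about 2 with two and essentially none with one. At n = 45 with four real it is about 5 to 6 points. The chance of finding at least one predictor is the same. These sizes rest on assumed equal correlations, two-sided tests and a correlation test in place of the mixed model. The dominance of Holm rests on none of these.

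**What to change.** In *Primary study parameter(s)* and *Other study parameters*, replace the fixed 0.05/4 rule with: *the predictor p-values are tested with Holm's step-down procedure at familywise alpha 0.05*. The four predictors and their models stay as they are. Make the change before the predictor data are analysed, so that it remains pre-specified.

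The cost is one sentence in two places, with no extra data or assumption. The one small downside is that simultaneous confidence intervals compatible with Holm are less simple than Bonferroni intervals. If such intervals are wanted, keeping Bonferroni is defensible.

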#### Secondary study parameter(s)

To investigate the effect of EMDR and waiting on secondary outcome variables (i.e. post-traumatic stress symptoms (CATS), anxiety symptoms (SCARED) and overall social-emotional problems (SDQ)), a mixed model analysis will be conducted. A chi-square test will be used to investigate whether there is a difference between the conditions in the percentage of MDD diagnosis (K-SADS-PL) at T1.

Effect sizes will be calculated using Cohen’s *d*. Based on the mean difference between scores from baseline (T0) to post-treatment (T1) and from baseline (T0) to follow-up (T2, T3), the results will be divided by the pooled standard deviation.

#### Other study parameters

For the prediction analyses, all treated participants, including participants from the former waiting list control group, will be combined. The four predictor variables (baseline post-traumatic stress symptom severity (CATS), emotional abuse, emotional neglect (CTQ) and general family functioning (FAD) scores will be entered separately in the linear mixed model analyses. Bonferroni post hoc corrections will be conducted in order to correct for the number of analyses. The level of significance will be set at *α* = 0.05/4.

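### The predictor set is inconsistent: Hypothesis 4 and the FAD description bring in seven family-functioning scores, but the 0.05/4 level counts only one of them

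*Protocol article*

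**What the plan says.** The two statements of the prediction analysis agree with each other. Under Other study parameters the article refers to "The four predictor variables (baseline post-traumatic stress symptom severity (CATS), emotional abuse, emotional neglect (CTQ) and general family functioning (FAD) scores". Under Primary study parameter(s) the family measure is again the general scale only: "emotional abuse and emotional neglect (CTQ), and general family functioning (FAD) on treatment outcome". That section adds "All predictors will be entered separately", so each score has its own test. Both sections give the same level: "The level of significance will be set at *α* = 0.05/4". The stated purpose is that "Bonferroni post hoc corrections will be conducted in order to correct for the number of analyses".

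Two other places describe a wider set. Under Objectives {7}, Hypothesis 4 gives its measure of the predictor as "family functioning (FAD, general functioning score and dimension scores". The Family functioning section lists six FAD dimensions and a seventh, general scale, and states: "Both dimension scores and the general functioning scale are used in the analyses". Hypothesis 3 uses one CATS score ("severity of post-traumatic stress symptoms (CATS total score"), and Hypothesis 5 uses the CTQ subscales for emotional abuse and emotional neglect.

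The article does not describe the FAD dimension scores as descriptive, supportive or exploratory. It gives no level for them other than the one for predictors in general.

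**The concern.** A Bonferroni divisor has to equal the number of tests in the family it protects. The protocol says the division is for the number of analyses, but that number depends on the section read: four in the statistical methods, ten in the hypotheses and the instrument description.

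Prediction is the trial's stated second aim, and Hypothesis 4 is a numbered, directional hypothesis. As the text stands, a report could test one FAD score or seven and cite the protocol for either. If a single dimension such as communication or roles reached p < 0.0125, it could be presented as confirming Hypothesis 4 under a correction that never counted it. A reader would then credit the result with 5% family-wise protection that it does not have.

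**Working it through.** **Inputs from the protocol article**

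- Level per test: 0.05/4 = 0.0125 (Primary study parameter(s); Other study parameters).
- Scores in the statistical methods: CATS 1, CTQ 2, FAD general functioning 1. Total 4.
- Scores in the hypotheses and the Family functioning section: CATS 1, CTQ 2, FAD 6 + 1 = 7. Total 10.
- One test per score, because predictors are entered separately.

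Ten is the count for one informant.

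**Formulas**, for m tests each at level a:

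- Upper bound on the family-wise error: m × a.
- Family-wise error under independence: 1 − (1 − a)^m.

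**The plan's own figure, m = 4, a = 0.0125**

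- Bound: 4 × 0.0125 = 0.050.
- Independence: 1 − 0.9875^4 = 0.0491.

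The stated level reproduces. For these four scores the correction does what it claims.

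**All ten scores at the same level, m = 10, a = 0.0125**

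- Bound: 10 × 0.0125 = 0.125.
- Independence: 1 − 0.9875^10 = 0.118.

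**Allowing for correlation.** Scales from one questionnaire are likely to be correlated, which lowers the family-wise error. The documents give no correlations, so the values below are assumptions. A simulation of 400,000 draws with two-sided tests gave the seven FAD statistics a common correlation, gave the two CTQ statistics the same correlation, and left CATS independent.

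| Assumed within-scale correlation | Ten tests at 0.0125 | Four tests at 0.0125 |
|---|---|---|
| 0 | 0.118 | 0.049 |
| 0.3 | 0.112 | 0.049 |
| 0.5 | 0.101 | 0.048 |
| 0.7 | 0.086 | 0.047 |
| 0.9 | 0.063 | 0.043 |

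Four tests stay below 0.05 throughout. Ten tests stay above it throughout, even at 0.9.

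**Level for ten tests**

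- 0.05/10 = 0.005.
- Bound: 10 × 0.005 = 0.050.
- Independence: 1 − 0.995^10 = 0.0489.

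**The case against.** The strongest reply is that the statistical methods define the tests, and that they do so twice with the same four predictors. For that family 0.05/4 is exactly right. The other two places attach no test and no level to the FAD dimensions: Hypothesis 4 lists them among its measures, and the Family functioning section says only that they are used. They could be meant as supportive description. The abstract also speaks of exploring whether these factors predict outcome.

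Much of this stands. A reader might infer that the Bonferroni correction is simply wrong and that the plan's error rate fails. The documents do not support that, because the excess arises only if the dimensions are also tested for significance at 0.0125.

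A reader might also infer a family larger than ten, since the CATS and the FAD are collected in child and parent versions. No section says that both versions will be tested as predictors, so that reading has no stated analysis behind it.

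The reply does not remove the contradiction. The dimensions belong to a numbered hypothesis, the article says they enter the analyses, nothing marks them as exploratory, and 0.0125 is the only level given for predictors. Two sections disagree about what a threshold covers, and this is more than a detail left to a fuller document.

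**Conclusion.** The point holds as an inconsistency in the predictor set, with a conditional effect on the error rate. The level 0.05/4 is correct for the four predictors named in the statistical methods. If all ten scores named in the hypotheses are tested separately at 0.0125, the family-wise error is bounded by 12.5% and equals 11.8% under independence. It falls to between about 11% and 6% under the assumed within-scale correlations of 0.3 to 0.9. These figures assume one informant, one test per score and true null hypotheses for all ten scores.

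Severity is low. Only the second-aim predictor analyses are involved, and the randomised comparison of EMDR with the waiting list is unaffected.

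**What to change.** Make Hypothesis 4, the Family functioning section and the two statements of the prediction analysis name the same set of scores. Either of two options would do.

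1. Keep 0.05/4 for the four named predictors. State in Hypothesis 4 and in the Family functioning section that the six FAD dimension scores are exploratory, reported with estimates and confidence intervals and without a claim of significance. The cost is that the dimensions lose confirmatory status; the four predictors lose no power.
2. If the dimensions are to remain hypothesis tests, list all ten scores in the statistical methods and set the level at 0.05/10 = 0.005. The cost is that the four predictors now tested at 0.0125 face the stricter level and lose power.

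Both options change wording only and need no new data. The first is the cheaper, because it leaves the stated level as it is.

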### Interim analyses {21b}

Not applicable, there are no interim analyses.

### Methods for additional analyses (e.g. subgroup analyses) {20b}

Not applicable, there are no subgroups.

### Methods in analysis to handle protocol non-adherence and any statistical methods to handle missing data {20c}

In case of treatment drop-out, we will try to motivate participants to adhere to the scheduled measurements. If this fails, we will still use data gathered from participants up until their withdrawal for the analyses. An intention-to-treat method will be performed.

Due to the randomized design, multivariable models will not be used to adjust for confounding, and therefore, the absence of covariates will not affect the primary analysis.

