### Trial design {8}

This study is designed as a randomized, controlled, single-blinded two-center superiority trial with two parallel groups. All patients meeting the inclusion criteria are asked for written informed consent to participate in the intervention study. For consenting participants, baseline measures (T0) are completed subsequently. Randomization will be performed as block randomization with a 1:1 allocation stratified per treatment location. An independent researcher will conduct randomized allocation by using the SPSS function to produce random numbers. Hence, the main researcher will be blind to the randomization process. Randomization will take place in blocks of 10 participants. After completing the baseline assessments (T0), participants will be informed in which group they have been randomized. Assessments (see Fig. 1) are scheduled pre-treatment (T0), post-treatment (T1), and at 3-month (T2) and at 6-month (T3) follow-up. Assessment will be done by a team of independent assessors (i.e. trained clinicians and supervised master level students) who are blind for condition. Participants in the waiting list condition are offered EMDR treatment after T1 and are subsequently assessed post-treatment and at 3 and 6 months follow-up (see Fig. 1). For participants in the waiting list condition, T1 will be labelled as T0WL when they enter treatment (*t*_*1*_ = *t*_*0-wl*_).

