## Assignment of interventions: allocation

### Sequence generation {16a}

Randomization will be performed as block randomization with a 1:1 allocation stratified per treatment location. An independent researcher will conduct randomized allocation by using the SPSS function to produce random numbers. To reduce predictability of a random sequence, details of any planned restriction (e.g. blocking) will be provided in a separate document that is only available to those who enrol participants and assign interventions. Hence, the researchers conducting the assessments will be blind to the randomization process. Randomization will take place in blocks of 10 participants.

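### Randomisation does not make covariates irrelevant to precision: the plan leaves the stratification factor out of the analysis and does not say whether baseline CDI-2 is used for adjustment

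*Protocol article*

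**What the plan says.** Section {20c} of the protocol article states that, given the randomised design, "multivariable models will not be used to adjust for confounding, and therefore, the absence of covariates will not affect the primary analysis". Trial design {8} describes a "single-blinded two-center superiority trial with two parallel groups" and allocates by "block randomization with a 1:1 allocation stratified per treatment location"; Sequence generation {16a} adds "Randomization will take place in blocks of 10 participants". Study setting {9} lists four locations at one institution and five at the other.

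For CDI-2 and the secondary scores, the section on primary study parameters says that "a linear mixed model analysis will be conducted". It gives neither the fixed effects nor the role of T0. Sample size {14} assumes "2 points of measurement (baseline and after treatment), the CDI-2 total score as outcome measure" and an "effect size of F = 0.40". Cohen's d is to be calculated as follows: "Based on the mean difference between scores from baseline (T0) to post-treatment (T1) and from baseline (T0) to follow-up (T2, T3"), divided by the pooled standard deviation. Location appears in none of the analysis sections.

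**The concern.** The sentence in {20c} draws a conclusion about the whole primary analysis from a premise about confounding only. In a randomised trial, covariates are used mainly to reduce the variance of the treatment estimate and to let the analysis reflect a stratified allocation. Neither reason goes away because confounding is absent.

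Two things are at stake. First, if a stratification factor predicts the outcome and is ignored, the model-based standard error tends to be too large. Second, an analyst who takes the sentence as policy has no reason to use baseline CDI-2 as an adjuster and may fit a model equivalent to a change-score comparison. The trial plans only 64 participants at an expected 1–3 per month, and both variables are already collected, so any avoidable loss of precision is worth preventing.

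**Working it through.** **The plan's own figure.** The protocol gives no figure for the effect of covariates, so there is none to reproduce on this point. Its 48 analysable participants (24 per group) serve below only as a sample size. That number does not follow from the stated inputs alone. With f = 0.40 and α = 0.05, a one-way comparison of two groups has power 0.774 at N = 48 and needs 84 for 0.95 (power is printed as 0.095, presumably meant as 0.95). Repeated-measures versions depend on a correlation that is not stated. None of this decides the covariate question.

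**Inputs.** n = 24 per arm and f = 0.40 come from {14}. Taking d = 2f = 0.80 for two groups is an assumption about what f refers to. The T0–T1 correlation r of CDI-2 is not in the document and is assumed at 0.3, 0.5 and 0.7.

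**Variance per participant, in units of SD².**
- Change score (arm by time, free T0 means, complete data): v = 2(1−r).
- T1 adjusted for T0, or approximately a mixed model with a common T0 mean: v = 1−r².
- Ratio, adjusted to change score: (1−r²) / [2(1−r)] = (1+r)/2.

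**Power.** Two-sided α = 0.05, noncentral t with noncentrality d / √(2v/n), and 2n−2 (change) or 2n−3 (adjusted) degrees of freedom. For r = 0.5 the noncentrality is 0.8/√(2×1.00/24) = 2.77 for change and 0.8/√(2×0.75/24) = 3.20 for the adjusted estimate.

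| r (assumed) | v, change | v, adjusted | ratio | power, change | power, adjusted |
|---|---|---|---|---|---|
| 0.3 | 1.40 | 0.91 | 0.65 | 0.63 | 0.81 |
| 0.5 | 1.00 | 0.75 | 0.75 | 0.77 | 0.88 |
| 0.7 | 0.60 | 0.51 | 0.85 | 0.94 | 0.97 |

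At r = 0.5, 48 participants analysed by change carry the information of 48 × 0.75 = 36 analysed with adjustment. Equivalently, the change analysis needs 1/0.75 = 1.33 times as many. If the mixed model already constrains the T0 means to be equal, the loss is about nil.

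**Location.** The nine listed locations would hold 64/9, or about 7, participants each. That is below the block size of 10, so blocks may not fill and balance within location is not assured. Location's share of the outcome variance is unknown. If it were 2 to 10% (assumed), adjustment would remove about that share of the variance. The price through the critical t value at N = 48 is a variance factor of about 1.001 with two strata (1 df) and 1.012 with nine (8 df).

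**The case against.** The sentence stands under missing data and speaks of adjusting for confounding. It may mean only that missing covariate values do no harm. That reading is possible, but it still implies that no covariates are planned, and it leaves the general claim about the primary analysis in place.

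A reader might infer that baseline CDI-2 is discarded. The document does not support this. The two measurement points in {14} and the mixed model both indicate that T0 is in the model as an outcome. The loss in the table therefore depends on free T0 means. The article states neither free nor constrained means, and such model detail is commonly left to the full protocol or analysis plan. This objection stands, and it makes the size conditional.

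The power figures also depend on d = 0.8. If f = 0.40 is the interaction effect in a 2×2 design, it corresponds to a difference in change of 4 × 0.40 = 1.6 SD. At r = 0.5 and N = 48 the change analysis would then have power above 0.99, leaving little power to gain. The variance ratio is unaffected.

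A reader might also infer that the planned Cohen's d mixes in natural recovery and regression to the mean. That holds if d is taken within an arm. If the changes are compared between arms, both cancel in expectation up to T1. The text does not say which is meant, and the question is separate from covariates.

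**Conclusion.** The statement that leaving out covariates will not affect the primary analysis is wrong as regards precision. It also sits badly with an allocation stratified by a factor that the analysis never mentions. That much rests on the text alone.

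The size cannot be fixed from the document. With free T0 means, adjustment would reduce the variance by 35, 25 or 15% for r = 0.3, 0.5 or 0.7; with a common T0 mean there is no loss. The gain from location is probably small.

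It would be tempting to say that the plan is biased, or that it definitely forfeits a third of its sample. Neither is supported. The unadjusted randomised comparison is unbiased, omitting the stratum tends to be conservative, and the one-third figure needs both r = 0.5 and free T0 means. The matter should be corrected because doing so is nearly free.

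**What to change.** Delete the claim in {20c} that the absence of covariates has no effect. State instead that CDI-2 and each secondary score are analysed with a linear mixed model with a common T0 mean for both arms (or T1 adjusted for T0), arm by time, and the stratification factor as a fixed effect. Report the adjusted between-arm difference at T1 with its 95% CI. Use institution (1 df) if the nine locations are too sparse; location itself would cost 8 df.

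For Hypothesis 1, base d on that between-arm T1 difference. Label the T0–T2 and T0–T3 values as within-group and descriptive, because waiting-list participants are offered EMDR after T1 and no untreated arm remains.

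The cost is wording and the stated degrees of freedom; no new data are required.
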